### Outcome measures

All outcomes will be measured by trained and experienced assessors from nursing and medical staff members, blinded to group allocation. With written consent to participate, patients were assigned an identification number (ID). The consent forms are kept in a locked cabinet for 10 years. All other data is stored via the hospital information system.

In cases of accident or injury, concerns of the medical staff members or unwillingness of patients to participate during the interventions, unblinding is permissible. For participants who suffer unexpected harm from trial participation receive medical care. The intervention will be modified immediately in response to harms or worsening patient’s conditions. If no improvement is achieved, the patient will be excluded from the study. Other criteria of discontinuing are, concerns of medical team members or if the patient withdraws his participation in the intervention. Adverse events related to the intervention are documented in detail.

Primary and additional outcome variables are presented in Table 2. The time points for the primary outcome measures are a maximum of 1 week pre- and post-intervention. The adherence to intervention and the documentation of adverse events will be recorded to investigate the feasibility of the exercise intervention. A potential relation of adverse events to the intervention will be evaluated by a senior old age psychiatrist, who is not part of the study team.

**Table 2 Tab2:** Objectives and instrumental set-up of the trial

	Variable	Instrument
**Primary outcome**	Depressive symptoms	CGI – Global improvement scale [34]
**Secondary outcome**	Depressive symptoms	BDI II [35] HAMD [36]
	Physical (in)activity	Body fixed Motion Sensor (McRoberts, The Hague, NL)
	Endurance performance	6-min walk test [37]
	Application of antidepressive medication	Fluoxetin equivalents (FED) [38]

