### Sample

Patients from two hospital wards will be screened for eligibility by a senior psychiatrist who is not involved in the study team. The inclusion and exclusion criteria are presented in Table 1. Written informed consent from the patient’s legal guardian or the patient was required. In accordance with the ethical approval and the task force on ethical and legal questions of the Association of Neuropsychopharmacology and Pharmacopsychiatry, the following consent for participation will be conducted [27]: With a score < 20 on the Mini-Mental Status Examination (MMSE) [27], the patient’s legal guardian was asked to give informed consent; for scores of ≥ 20 and the ability to explain the content and aims of the project in the patient’s own words, the patient was considered to be able to give the informed consent on its own.

**Table 1 Tab1:** Inclusion and exclusion criteria

Inclusion criteria	Exclusion criteria
Diagnosis of depression according to ICD-10 (F31.3–F34)	Clinical exclusion of delirium (based on CAM); combined diagnosis of depression and an alcohol-induced neurodegenerative disease
Minimum length of stay of 3 days before enrollment in the study	Acute and/or severe cardiac disorder, neurological disease, and/or chronic orthopedic disorder
MMSE ≥ 19 points and the ability to explain the content of the study in the patients’ own words^a^	MMSE < 19 points
Prescription for exercise therapy (this includes cardiovascular capacity)	

*ICD-10* International Statistical Classification of Diseases and Related Health Problems, *CAM* confusion assessment method [28], *MMSE* Mini-Mental Status Examination, maximum score of 30 points, higher score indicating better cognitive functioning

^a^This approach is consistent with the Society for Neuropsychopharmacology and Pharmacopsychiatry Working Group on Ethical and Legal Issues [27]

As part of routine care, baseline characteristics are recorded within the geriatric assessment, which is carried out by a nursing and medical staff member of the LVR-Hospital Cologne. The geriatric assessment includes sex, age, weight and height, clinical diagnosis, MMSE [29], and Timed Up and Go Test (TUG) [30].

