### Primary outcome

The primary outcome of the intervention is the change in depressive symptoms rated by the clinical global impression of change (CGI). The CGI is performed by the clinician and includes a 1- to 7-point rating scale of the global improvement due entirely to treatment [34].

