### Secondary outcomes

As a secondary outcome, the symptom domains and the severity of depressive symptoms will be measured by self- and peer-rated assessments. The Beck Depression Inventory (BDI II) [35] is a self-rated scale which is conducted with the patient in interview form. The Hamilton Rating Scale for Depression (HAMD) [36] is performed by the nursing staff members. Mobility-related measurements, such as physical in(activity), will be performed with the Dynaport Move Monitor + (MM+; McRoberts, The Hague, NL). The MM+ consists of an accelerometer, a gyroscope, a magnetometer, a barometer and a temperature sensor. The raw data will be processed using the manufacturer’s own algorithms. The corresponding output includes the type of activity and body positions (walking, stair walking, cycling, shuffling, standing, sitting, and lying) and an additional category not-worn, corresponding MET-values, activity duration, and number of steps per 60-s epoch. Data will be collected for a 48-h period, starting and ending at 12 am on days one and three. The sensor is attached to the lower back approximately 3 cm to the right of the fifth vertebra of the lumbar spine (L5) with a waterproof self-adhesive foil (Opsite Flexifix, Smith and Nephew, London, UK) [39]. The participants will be asked not to remove the sensor during the measurement period.

To assess the endurance performance, the 6-min walk test [37] will be performed at pre- and post-assessment. The patients will be asked to walk a maximum distance in 6 min. The walking speed can be determined by the patient himself and changes and breaks will be allowed.

The applied total dose of antidepressant medication will be assessed by converting the fluoxetin equivalent doses (FED) and the medication on demand in mg/day according to the dose equivalents calculation of Hayasaka et al. [38].

The phases of the trial and the data collection at each timepoints are presented in Fig. 2.

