### Intervention

#### Intervention group

Participants allocated to the IG will receive a 2-week ergometer-based aerobic exercise three times per week on non-consecutive days and a duration of 20 min, twice per day. The training can be completed using four different modalities, seated-ergometer bicycles for the upper or lower limb (Emotion Fitness, Inc., USA), rowing ergometer (Concept 2, Inc., USA), or ski ergometer (Perform Better Inc., USA) placed on the hospital wards. This approach is planned to provide low-threshold access and variety in exercise selection, allowing participants to choose a preferred style of moving at each session to complete the weekly requirements. If the patient refuses or is hindered for any reason, the patient is asked to participate once again on the same day. The adherence to the intervention will be recorded by study reports and the training intensity will be monitored by the heart frequency (Polar A300, Polar Electro Oy, Finland).

The training will be performed individually and under constant supervision by research staff. Patients will be instructed on the adequate use of exercise machines before and during each training session. The participant will receive a fitness and activity tracker with a heart rate (HR) monitor (Polar UNITE, Polar Electro Oy, Finland) and be asked to rate the perceived exertion (RPE) with the 6-20 Borg Scale [40] after 10 min (half time of intervention) and after 20 min (end of intervention). The respective training HR will be determined using the formula 220 minus the patient’s age [41]. Each session will begin with a 2 min warm-up of ergometer use with a HR under 50% of the estimated peak heart rate. After 3 min, the participant will be asked to increase the intensity up to 55% of the estimated peak heart rate. After 18 min, the participants will be instructed to decrease the intensity to their own wish to initiate the cool-down. The research staff will collect the exercise data from each session, including the total time of training, average HR and Borg Scores.

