## Discussion

The primary aim of this study is to investigate the effect of aerobic exercise in older adults with major depression in acute geriatric psychiatry. Meta-analyses reported only a few adverse events in older adults during ergometer-based aerobic training [26]. We expect a corresponding adherence to the training intervention, due to exercise sessions conducted on the wards and multiple exercise sessions within an exercise day. Based on the previous research of positive effects in middle-aged adults with clinical depression [22] and the positive outcomes of aerobic exercise with older adults [25], we assume the feasibility and a significant change in depressive symptoms, due to a number of mechanisms of action, such as hormonal changes, effects on neurogenesis, inflammation and oxidative stress [25].

This single-center randomized controlled trial will be the first, to the best of our knowledge, to evaluate a short-term aerobic exercise on different ergometers in a hospital-based setting with older adults suffering from clinical depression.

The short duration of 2 weeks is derived from the median length of stay in the hospital of 32 days in older inpatients with depression [14]. The intervention takes place on the wards of a geriatric psychiatric unit and will begin no earlier than 3 days after admission to allow patients to acclimatize. This schedule seems feasible to include most patients and preserve a low dropout rate due to early discharges.

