A serious issue in the hospital setting is the high level of physical inactivity among inpatients [43, 44]. A recent umbrella review indicates that higher physical activity levels in older adults have a 21% reduction in incident depression compared to older adults, who have lower levels of physical activity [45]. Physical inactivity leads to other risk factors such as sarcopenia [46, 47], loss of independence [48], and disability in ADL [49, 50]. Recent recommendations during hospitalization suggest that older inpatients should be as active as possible and incrementally enhance movement in everyday activities [51]. In addition, it is recommended that the influence of the physical environment should also be considered to enable older people to be active with portable adaptations and equipment for indoors and outdoors [51]. For this study, new types of ergometers will be placed on the wards to facilitate an environment that promotes exercise. From our point of view, this could counteract the loss of interest and decreased impulse known as key aspects in exacerbated periods of major depression. From our clinical experience, the variety of ergometers should increase the patients’ willingness for participation. It also offers advantages, for example when patients experience fatigue or pain in the lower limbs, they can still exercise while sitting on the ski ergometer. Therefore, this type of study is an important opportunity to strengthen physical activity in standard treatment.

This will be the first single-blinded RCT to examine physical interventions for the treatment of depression in an acute hospital setting. The outcomes of this trial can be directly transferred and implemented in the hospital. In order to include as many acute geriatric patients as possible, the inclusion criteria were chosen to include patients with mild cognitive impairment and bipolar disorder with depressive episodes.

Some limitations must also be considered; diverse factors in the TAU process could influence the success of decreased depression symptoms. The TAU, especially the pharmacological therapy, is expected to be effective in the treatment of depression symptoms. Another limitation is that the severity of depression symptoms, for example, a minimum score of the HAMD, is not an inclusion criterion. This study will be conducted in a geriatric psychiatry unit, where all of the included patients have a clinical diagnosis of depression, so symptom severity can be assumed.

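### Unblinding is allowed for reasons other than safety, and nothing stated keeps the CGI and HAMD raters out of it, so the subjective primary rating is at risk

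*Protocol article*

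**What the plan says.** Protocol article, Methods, Outcome measures: "All outcomes will be measured by trained and experienced assessors from nursing and medical staff members, blinded to group allocation". The next paragraph sets the unblinding rule. It names accident or injury first and continues: "concerns of the medical staff members or unwillingness of patients to participate during the interventions, unblinding is permissible". It does not say who learns the allocation, who decides, or whether an assessor who learns it goes on rating that patient.

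On the ratings themselves, Primary outcome says: "The CGI is performed by the clinician and includes a 1- to 7-point rating scale of the global improvement due entirely to treatment". Under Secondary outcomes, the HAMD "is performed by the nursing staff members".

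On location, the ergometers are "placed on the hospital wards" (Intervention group), and the Discussion says: "The intervention takes place on the wards of a geriatric psychiatric unit". Patients come from two wards (Sample). Research staff supervise every session (Intervention group).

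On the label, the Discussion says: "This will be the first single-blinded RCT".

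**The concern.** Patients and trainers in an exercise trial cannot be blinded, so the protection rests on the assessor. Assessors are the only people whom the article names as blinded. The primary outcome needs that protection more than most. It is one global judgement on a 1-to-7 scale, and the rater is asked how much of the improvement is attributable to treatment. A rater who knows the arm, or knows that the patient declined the sessions, has information that bears directly on that judgement.

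An exception for emergencies is normal. This one reaches further, to ordinary refusals and to staff concerns of any kind, and those concerns arise in the same professional groups that supply the raters. If unblinding follows refusal and refusal differs between arms, the measurement error differs between arms too. The HAMD, the main clinician-side secondary measure, shares the exposure because nursing staff rate it.

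**Working it through.** The article gives no expected number of refusals or unblindings, so there is no planned figure to reproduce. The check is mainly a reading of the sections against each other.

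1. **Is unwillingness a safety ground?** No. Outcome measures lists it separately from accident or injury. The staff-concern ground has no stated limit to safety either.

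2. **Is it expected to occur?** Yes. The Abstract singles out illness-related motivation to exercise as the greatest difficulty. The regimen offers 2 sessions a day × 3 days a week × 2 weeks = 12 sessions per intervention patient, so there are many occasions for a refusal.

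3. **Does handling a refusal require unblinding?** No. Under Intervention group, a patient who refuses is simply asked again on the same day. Research staff run the sessions and know the arm.

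4. **Does it come before the rating?** Yes. The ground applies during the intervention, and the post-intervention assessment follows.

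5. **Do the affected ratings enter the analysis?** Where they are obtained, yes. Analysis keeps all patients with baseline data under intention to treat. Some unwilling patients may leave the study (withdrawal is a discontinuation criterion in Outcome measures) and never be rated, so not every such case would carry an unblinded rating.

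6. **Is the rater separated from the process or from the sessions?** Nothing stated does so. Raters come from the nursing and medical staff. The ergometers and sessions are on the wards, and the control activity (seated relaxation and flexibility) looks different from ergometer training. The article does not say on which ward the raters work.

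**Illustration only.** Inputs: 50 patients per arm (Sample size calculation) and two-sided α = 0.05. Two further inputs are assumptions and appear nowhere in the article: q, the share of one arm rated unblinded, and b, the shift in those ratings in SD units, all in one direction. With outcome SD 1 and a normal approximation:

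- Standard error of the difference = √(2/50) = 0.2
- Mean bias = q × b
- Type I error = Φ(5qb − 1.96) + Φ(−5qb − 1.96)

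| q | b | Bias (SD) | Type I error |
|---|---|---|---|
| 0.1 | 0.3 | 0.03 | 0.0351 + 0.0174 = 5.3% |
| 0.2 | 0.25 | 0.05 | 0.0436 + 0.0136 = 5.7% |
| 0.3 | 0.5 | 0.15 | 0.1131 + 0.0034 = 11.7% |
| 0.5 | 0.5 | 0.25 | 0.2389 + 0.0007 = 24.0% |

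The result runs from almost nothing to serious, depending wholly on q and b. If unblinding occurs in both arms, the net bias is the difference between the arms' q × b, and equal shifts in the same direction cancel. If raters mark down refusers in the intervention arm, the sign reverses: a shift of −0.15 SD would turn the assumed effect of 0.5 into 0.5 − 0.15 = 0.35, which costs power and does not create a false benefit.

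**The case against.** The other side has several fair points.

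- **The rule permits unblinding and does not require it.** A refusal need not lead to one. This stands, so the rule creates an opportunity and not a certainty.
- **The recipient is not named.** It could be a treating physician who does not rate, or the senior psychiatrist outside the study team who judges whether adverse events are related to the intervention. A reader might infer that it must be the outcome raters, since they are the only people named as blinded. The text does not establish that. It also does not exclude it, and this is the defect.
- **A reader might infer that the raters are staff of the wards where the ergometers stand.** The article says only nursing and medical staff. It places them neither on those wards nor elsewhere.
- **A reader might infer that refusals fall mainly in the intervention arm.** This is plausible, because the control activity is very light, but no split is given. Control patients can also refuse, and the Discussion expects the choice of ergometers to help willingness.
- **A condensed article leaves operational detail to the full protocol.** This holds for logging procedures and rater rotas, and their absence alone would be no finding. It does not cover the ground itself: the article states that unwillingness permits unblinding, and that is a stated rule that is too broad.

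**Conclusion.** The point holds as a risk to the blinding. The stated grounds go beyond safety, and nothing stated keeps the CGI and HAMD raters out of the unblinding process or away from the sessions on the wards. The bias has unknown size and direction.

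Two stronger conclusions are not supported. One is that the trial is not single-blind at all: blinded assessment is stated and research staff run the sessions, so a permissive exception endangers the label without making it false. The other is that the false-positive rate rises to some particular level, such as the 24.0% in the last row above: that figure follows from assumed inputs and a shift in one direction only.

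The point rests on two readings: that the rule applies as written, and that the full protocol does not narrow it. It is worth amending because the change costs little and protects the primary outcome. When Protocol Version 1.2 was dated, 15 of 100 patients had been recruited, so 100 − 15 = 85 were still to come.

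**What to change.** 1. Remove unwillingness as a ground for unblinding, and limit the staff-concern ground to safety.
2. Where safety requires unblinding, tell only the treating clinician. A still-blinded assessor from existing staff then rates CGI and HAMD for that patient, preferably someone who does not work on the patient's ward, where the rota allows.
3. Record each unblinding by arm, with its reason and its timing relative to the rating.
4. Keep all patients in the intention-to-treat primary analysis. Unblinding happens after randomisation and may be tied to non-adherence, so leaving out unblinded ratings could selectively remove refusers from one arm. Any such analysis should be labelled exploratory.

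The cost is a wording change, a short log and some scheduling effort. Substitute raters may know the patient less well, which could make a global rating of change somewhat noisier. Unblinding after accident or injury stays available. Whether the rota allows raters from outside the patient's ward is for the site to confirm, because the article does not describe ward staffing.

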### Allocation

With an informed consent and pre-assessment, randomization will be performed via stratified randomization. An organizational staff member, who is not part of the study team, will perform the group allocation. Study randomization was done through Study Randomizer (2017), a web-based randomization service [33]. In order to achieve the best possible balance between the two study groups, the factors, sex, age, and MMSE score [29] will be weighted 1:1 in the program. Patients are sequentially numbered, no conclusion can be drawn about the patients, with the exception of the study director who takes the patient's informed consent.

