### Analysis

The trial will be analyzed by using the intention-to-treat principles, in which all patients with baseline data are included in the analysis. Adherence to intervention will be collected descriptive at each training session. The data are stored on the clinic’s own servers, which comply with a heightened security system. Missing data that are not directly related to adherence will be imputed, in order to include all participants. Differences between IG and CG from baseline to post-intervention will be determined by one-way repeated measure ANOVA for parametric and normally distributed data or the Friedman one-way repeated measure analysis of variance for non-parametric or non-normally distributed data. The level of significance is set at alpha ≤ 0.05. All computations will be performed using SPSS software (IBM Corporations, Armonk, NY, USA). No committee for data monitoring and auditing is planned.

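### A post-randomisation rule excludes patients from the study after an unresolved harm or worsening, which conflicts with the intention-to-treat analysis and can leave poor outcomes uncollected

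*Protocol article*

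**What the plan says.** Randomisation comes after consent and baseline assessment (Allocation): "With an informed consent and pre-assessment, randomization will be performed via stratified randomization".

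The Outcome measures section then sets out what happens during the programme. First, "The intervention will be modified immediately in response to harms or worsening patient’s conditions". Next, "If no improvement is achieved, the patient will be excluded from the study". Then, "Other criteria of discontinuing are, concerns of medical team members or if the patient withdraws his participation in the intervention". Nothing there says whether a patient who is excluded or discontinued still has the post-intervention assessment.

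The Analysis section applies "intention-to-treat principles, in which all patients with baseline data are included in the analysis". It adds a rule for missing values: "Missing data that are not directly related to adherence will be imputed, in order to include all participants".

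The primary outcome is the CGI, which "includes a 1- to 7-point rating scale of the global improvement due entirely to treatment".

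**The concern.** Patients who are harmed or get worse during the programme, and do not recover once it is modified, are the ones likely to include poor ratings on a scale of global improvement. Excluding them from the study after randomisation can take those ratings out of the data. An intention-to-treat statement cannot bring back an outcome that was never collected.

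The CGI improvement item makes this harder to repair. It is itself a rating of change, so there is no baseline value of the same item to carry forward.

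If such exclusions are more common in one arm, the patients left in that arm look better than the group that was randomised to it. The comparison then no longer rests on randomisation alone.

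**Working it through.** **Passages side by side**

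1. *Timing.* Allocation follows the baseline assessment. The exclusion follows an event during the intervention. Every excluded patient is therefore already randomised and has baseline data.
2. *Analysis set.* The Analysis section includes everyone with baseline data. An excluded patient belongs in that set, yet the Outcome measures section puts the same patient outside the study. Both cannot be followed as written.
3. *Imputation.* Two groups need separating.
   - Outcome missing because of harm or worsening: on a plain reading this is not directly related to adherence, so it would be imputed. Values modelled from patients who were not excluded may be too favourable for patients removed because of a poor course.
   - Outcome missing because the patient stopped exercising: this is plausibly adherence-related and so falls outside the rule. If the post-assessment is not done either, the outcome is neither collected nor imputed.

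**Size of the possible bias**

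The plan has no figure of its own to reproduce here. From the Sample size calculation section come 50 patients per arm, a two-sided alpha of 0.05 and a planning effect of 0.5 SD. Assumed, because the article gives nothing: the numbers excluded in each arm, and how closely exclusion follows outcome.

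*Closed form.* Take no true effect, a normal outcome, and the worst fraction q removed from the exercise arm only. With z the q-quantile of the standard normal:

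- mean shift b = φ(z)/(1 − q)
- variance of the remainder v = 1 + z·b − b²

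For q = 0.10 (5 of 50): z = −1.282, φ(z) = 0.1755, so b = 0.1755/0.90 = 0.195 SD and v = 0.712. The standard error is √(0.712/45 + 1/50) = 0.189, and b/SE = 1.03. The false-positive rate is Φ(1.03 − 1.96) + Φ(−1.03 − 1.96) ≈ 0.176 + 0.001 ≈ 18%.

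*Simulation.* 20,000 null trials per cell. Each patient gets an exclusion score ρ·outcome + √(1 − ρ²)·noise. The lowest k in each arm are dropped and a two-sided t-test is run on complete cases. ρ = 1 removes exactly the worst responders and is an upper bound. Cells show the spurious benefit in SD and the false-positive rate.

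| Excluded, exercise v control | ρ = 1 | ρ = 0.5 | ρ = 0.3 |
|---|---|---|---|
| 5 v 0 | +0.19, 18% | +0.095, 8% | +0.06, 6% |
| 10 v 5 | +0.15, 18% | +0.07, 7% | +0.05, 6% |
| 8 v 2 | +0.20, 21% | +0.10, 8% | +0.06, 6% |
| 2 v 1 | +0.04, 7% | +0.02, 6% | +0.01, 5% |
| 5 v 5 | 0, 8% | 0, 5.5% | 0, 5% |

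A repeat run of the 8 v 2 case at ρ = 1 gave 22%. In the 5 v 5 row the mean bias is zero; the 8% at ρ = 1 arises because the t-test understates the variance after trimming.

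*Ordinal check.* I assumed a 7-point distribution with 20% of patients rated worse, excluded half of those from the exercise arm only (10% of the arm), and used a Mann-Whitney test. The spurious effect was d = 0.19 with 11% false positives. The shift matches the 5 v 0 upper bound, with a smaller excess of false positives.

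The range for the first three rows, 0.05 to 0.20 SD, is 10% to 40% of the planning effect (0.05/0.5 and 0.20/0.5).

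**The case against.** Several points can be made for the plan, and most of them limit the concern.

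- *Scope.* A reader might infer that anyone who stops exercising leaves the study. The exclusion wording attaches only to non-improvement after harm or worsening. Team concerns and withdrawal are listed as reasons for discontinuing, which may mean the intervention alone. This stands: for those patients the text is ambiguous, not plainly wrong.
- *Who is lost.* A reader might infer that every patient rated unchanged or worse is removed. The rule does not say that. It needs a prior harm or worsening, and the paragraph also deals with accident and injury. A patient whose CGI is unchanged and who had no such event stays in, and a patient excluded for an injury need not have a poor CGI. This stands, and it is why ρ = 1 is only an upper bound.
- *Imputation.* The plan does intend to impute in order to keep all participants. This stands in part: harm-related gaps are probably covered, so the complete-case figures overstate the bias for that group. The adherence exception still leaves the other group open.
- *Direction.* A reader might infer that the bias favours exercise, since the control is very low-intensity. The article gives no rates by arm and applies the rule to both. The Discussion cites few adverse events with ergometer training. If exercise helps, worsening could be more common among controls and the bias would run the other way. This stands.
- *Condensed article.* The full protocol may describe follow-up after discontinuation. It may, but the two statements printed here still conflict.

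**Conclusion.** The conflict is real. The plan states a post-randomisation exclusion from the study that depends on a poor course, beside an intention-to-treat analysis of all patients with baseline data. It does not distinguish stopping the intervention from leaving the study, and its imputation rule may leave out those who stop exercising.

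The effect on the result is conditional. Bias in the mean arises only if exclusions are related to outcome and unequal between arms. Under the assumed imbalances of 5 v 0, 10 v 5 and 8 v 2, with complete cases and no true effect, it is about 0.05 to 0.20 SD with a false-positive rate of about 6% to 22%. With 2 v 1 excluded it is at most about 0.04 SD and 7%, and with equal numbers there is no mean bias. The documents do not support a claim that the trial is biased towards exercise, or by any particular amount. They support the claim that the plan, as worded, allows such a bias and does not prevent it.

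**What to change.** Reconcile the Outcome measures and Analysis sections by amendment, leaving the clinical rules for modifying or stopping the intervention as they are.

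1. In Outcome measures, replace the exclusion from the study with *discontinued from the intervention*.
2. Add: *Stopping or modifying the intervention for any reason does not end participation. CGI, HAMD and BDI-II are collected at the planned post-assessment for every randomised patient unless consent to data collection is withdrawn. All patients are analysed in the arm to which they were allocated.*
3. In Analysis, remove the adherence exception, so that the imputation rule covers every outcome that is still missing.

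The cost is a few sentences and a few more post-ratings. Most should be possible on the ward, since the Discussion gives a median stay of 32 days against a 2-week programme, but some patients will need to be rated after discharge. Outcomes that were not collected cannot be recovered later, and recruitment has already begun, so the change is best made promptly.
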